## **7.2 Study drug**

### **(1) Drug information**

- Drug: Mycophenolate mofetil (MMF)
- Formulation: Mycophenolate mofetil tablets 0.25g/tablet
- Manufacturer: Hangzhou Zhongmei Huadong Pharmaceutical Co., Ltd

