## **7.3 Concomitant medication**

Participants in this study, whether in the MMF or control arm, will all receive supportive care for IgA nephropathy. The investigator should strive to control the blood pressure to a target of 130/80 mmHg. Throughout the trial, all participants should receive losartan adjusted to the maximal tolerated dose. All participants will have dietary recommendations for CKD, e.g. Low-salt intake (<5 g per day). Participants will be advised to quit smoking and limit alcohol intake during the study as part of standard supportive care. Anemic patients with a hemoglobin level lower than 110g/L were treated with erythropoietin. Statins will be recommended when necessary. Dietary sodium intake

were monitored by urinary sodium excretion rate (or chloride excretion rate in patients treated with sodium bicarbonate) measured by 24-hour urine sample.

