**Treatment period**

**Visit 6-18**

Patients who are assigned to the MMF group will received oral administrated MMF at a daily dose of 1.5g for 12 months and then tapered to a maintained daily dose of 0.75g to 1.0g for at least 6 months. Patients who are assigned to the supportive care group will stay on supportive care as in run-in period. Participants will receive routine follow-up every 4 weeks in the first 6 months and then every 8 weeks.

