### Analysis sets

1. ITTs (Intention-to-test set): All enrolled subjects who sign the informed consent and undergo randomization. ITTs will be used for all efficacy analyses
2. SS (Safety set): All enrolled patients who have used the study drug. The SS set will serve as the primary analysis population for all safety outcomes.

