## 3.2. Study Drug

### Drug information

- Drug: Mycophenolate mofetil
- Formulation: Mycophenolate mofetil tablets 0.25g/tablet
- Manufacturer: Hangzhou ZhongmeiHuadong Pharmaceutical Co., Ltd

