### **5.2. Safety Set (SS)**

SS is a subset of ITT. It consists of ITT participants excluding the ones without taking any study medication or having no record of follow up after randomization. SS will be used for the safety analysis.

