### **6.4. Safety Analysis**

The analysis of safety endpoints will be performed on the SS. For safety analysis, no formal hypothesis testing will be performed. Descriptive analysis will be performed to summarize safety events. Serious adverse events and adverse events will be summarized as the number of events and the number (%) of patients experiencing at least one event. Differences in the proportions of patients experiencing at least one event will be tested using Fisher's exact test.

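### Read literally, the safety set admits only patients who took MMF. This contradicts the two-arm safety analyses ordered on it, and the same condition recurs in the AE window and AE documentation rule

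*Combined protocol and SAP*

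**What the plan says.** **Who is in the set.** Protocol 7.12 (Analysis sets) defines it as: "All enrolled patients who have used the study drug. The SS set will serve as the primary analysis population for all safety outcomes". SAP 5.2 derives it from the efficacy set as follows: "It consists of ITT participants excluding the ones without taking any study medication or having no record of follow up after randomization".

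**What the study drug is.** SAP 3.2 has one entry, "Drug: Mycophenolate mofetil", and protocol 7.2 also lists MMF alone. Losartan appears in protocol 7.3 under concomitant medication: "Throughout the trial, all participants should receive losartan adjusted to the maximal tolerated dose". For the control arm, protocol 7.9 (Visits 6-18) says: "Patients who are assigned to the supportive care group will stay on supportive care as in run-in period". No placebo is described.

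**What is done on the set.** SAP 6.4: "The analysis of safety endpoints will be performed on the SS". That section orders Fisher's exact test on the proportions of patients with at least one event. SAP 6.4.2 adds laboratory plots by randomised group and a mixed model with treatment, time and their interaction.

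**Which events count.** SAP 3.7.1 analyses AEs and SAEs from the first MMF dose to 30±7 days after the last. Protocol section 9 (Collection) opens by requiring AEs to be documented after enrolment, then waives this for any patient who has not taken MMF. Table 1 in both documents schedules AEs/SAEs at Visits 3 to 28 with no restriction by arm, and protocol 7.7 (Safety endpoints) records AEs over the study period.

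**The concern.** A safety set defined by exposure works in a placebo-controlled trial, where each arm has a study medication to take. Here only one arm does. A programmer who applies the rule as written builds a one-arm set and then meets instructions to compare two arms on it.

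The stake is the randomised comparison of harms. The events of special concern include leukopenia, infections, hepatic dysfunction and malignancy. These can occur without MMF, so the rate in the MMF arm cannot be read as drug harm without a concurrent control rate. If the text is left alone, someone has to decide later which controls and which of their events count, in a trial where patients and study personnel know the allocation.

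The documentation waiver is the more serious part. A set definition can be corrected up to database lock. Control-arm events that were never written down cannot be recovered.

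**Working it through.** **1. Arm size.** The documents give no size for the safety set, so the planned arm size is used (protocol 7.4: 36% versus 16%, two-sided 0.05, power 80%, 76 per group, 84 after 10% loss). Check with n = [z(0.975)·√(2·p̄·q̄) + z(0.80)·√(p1·q1 + p2·q2)]² / (p1 − p2)², where p̄ = 0.26:
- 1.960 × √0.3848 = 1.216, and 0.842 × √0.3648 = 0.508.
- (1.216 + 0.508)² / 0.20² ≈ 74.3, so 75 per group against 76 stated. Power at 76 is 0.809.
- 75 / 0.90 = 83.3, rounded up to 84, as stated.

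With 1:1 allocation, 2 × 84 = 168 patients are planned.

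**2. Apply the literal rule.**
- MMF arm: up to 84 qualify (at least one dose; in the SAP also a follow-up record).
- Supportive-care arm: 0 of 84 qualify, because none is given MMF.
- The rule leaves out 84/168 = 50% of planned patients, all from one arm.

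**3. Run the planned tests on that set.**
- *Fisher.* The table is [x, 84 − x] over [0, 0]. Its margins allow only one table. For x = 1, 20, 40 and 84 the result was p = 1.0 with an undefined odds ratio each time. Software runs it, but the p-value says nothing and could be misread as no difference.
- *Laboratory model.* Treatment equals 1 in every row, so its column duplicates the intercept and the interaction columns duplicate the time columns. Neither effect is estimable.

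**4. Test the losartan reading.** If study medication in SAP 5.2 includes losartan, controls stay in. SAP section 2 gives some support, since its objective compares MMF plus losartan with losartan alone. Against it:
- Losartan is filed under concomitant medication.
- Protocol 7.2(3) uses study medications and study drug interchangeably for the counted tablets.
- Table 1 dispenses study drug only at Visits 6 to 18 (to week 78), the visits under which the MMF course is described, whereas losartan runs throughout.
- All patients are treated with losartan in the run-in, so the medication clause would exclude nobody. The no-follow-up clause would still exclude some patients, so this last argument is not decisive.
- Protocol 7.12 says study drug, so this reading cannot rescue it.

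**5. The AE window.** A control has no first or last MMF dose, so SAP 3.7.1 gives no window. For an MMF patient, assume the last dose is at week 78. The window then closes at 78 + 30/7 = 82.3 weeks (81.3 to 83.3 with the ±7 days), leaving 156 − 82.3 = 73.7 weeks of follow-up outside it. Maintenance is specified only as a minimum, so later closing dates are possible.

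**6. With both arms restored (up to 84 versus 84).** Exact power of Fisher's test at two-sided 0.05, using assumed AE rates that are not in the documents: 10% versus 5%, 0.15; 20% versus 10%, 0.37; 30% versus 10%, 0.88.

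**The case against.** The strongest reply is that the plan plainly intends two arms. Fisher's test on differences, the plots by randomised group, the treatment-by-time model and the 0.05 threshold for safety analyses in SAP 4.4 make no sense otherwise. SAP 5.2 uses a term that it does not define, and SAP section 2 treats losartan as the comparator treatment. Haematology and chemistry are scheduled for every patient, so control laboratory values such as white cell counts and transaminases should exist whatever the analysis set is called. Primary efficacy is analysed on ITT and is untouched.

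Much of this stands. A reader might infer that half the trial will be dropped from the safety analysis, or that harm data will exist for the MMF arm only. The documents do not support either inference. The 50% follows from one literal reading, two-arm intent is evident, and the laboratory data are scheduled regardless of arm. A reader might also picture a control who crosses over to MMF as the only control in the set, but neither document provides for controls to receive MMF.

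Intent does not repair the text, however. The protocol's wording admits no second reading, and the same MMF condition recurs in the AE window and the documentation waiver, so this is not a single slip of wording.

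**Conclusion.** The point holds as a contradiction within the plan that must be corrected. Taken literally, the safety set holds up to 84 MMF patients and 0 of 84 planned controls, while SAP 6.4 and 6.4.2 order between-arm analyses on it. On that set Fisher's test is uninformative and the laboratory treatment effect is not estimable. SAP 3.7.1 and the waiver in protocol section 9 carry the same condition, and the waiver also conflicts with Table 1 and protocol 7.7.

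This rests on MMF being the only study drug, which both study-drug sections state, and on planned rather than observed numbers. It does not show that controls will be left out. Whether control-arm AEs were in fact collected cannot be determined from the documents.

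**What to change.** 1. **Safety set (protocol 7.12 and SAP 5.2, same wording).** Define it as randomised patients with at least one post-randomisation follow-up record who, in the MMF arm, took at least one dose of MMF. Set no study-medication condition in the supportive-care arm. State one grouping rule and use it in both SAP 6.4 and 6.4.2; 6.4.2 already plots by randomised group.
2. **AE window (SAP 3.7.1).** Start at randomisation (Visit 5) and end at the same point in both arms, for example the last scheduled visit at week 156. Keep the MMF-anchored window only as a descriptive on-treatment summary for the MMF arm.
3. **Documentation (protocol section 9, Collection).** Reconcile the waiver with Table 1 and protocol 7.7 so that AEs and SAEs are documented in both arms from randomisation. If control AEs were not systematically collected under the waiver, state this as a limit on the AE comparison.

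The three changes belong together. Changing the set alone would put controls in the denominator while their events need not be recorded, which would bias the comparison against MMF.

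The cost is a few more lines in each document. The main AE summaries will also include events after MMF has stopped, which is why the on-treatment summary is kept alongside.

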## **6. Statistical Analyses**

### **6.1. Population Characteristics at Randomization**

The demographic and clinical characteristics of the ITT set at randomization stratified by the treatment group will be summarized. Summary statistics for quantitative variables will include N, mean, SD, or median, Q1, Q3. Summary statistics for qualitative variables will be N (%) for each level. Unless otherwise specified, the calculation of proportions will be based on the non-missing data. Difference in the variable distribution between the two treatment groups will be tested using the unpaired two-sample t-test (quantitative variables) and the chi-square test (qualitative variables). The following variables will be analyzed:

- Demography: age, sex, BMI.
- Comorbidity: smoking status, macrohematuria, history of hypertension, other reported medical history and co-morbidities.
- Vital Signs: body temperature (°C), pulse (beats/min), blood pressure (mmHg), respiratory rate.
- Use of Medications: anti-hypertensive drugs and types; statin.
- Baseline serum creatinine and eGFR. The baseline creatinine is calculated as the mean of the two creatinine values from Visit 4 (pre-randomization visit) and Visit 5 (randomization visit). Baseline eGFR is calculated from baseline serum creatinine using the CKD-EPI equation
- Other laboratory results:
  - Hematology: hemoglobin, white blood cell count, lymphocyte and platelet count
  - Blood chemistry: urea nitrogen, uric acid, total carbon dioxide, potassium, sodium and chlorine, alanine aminotransferase, aspartate aminotransferase, albumin, total bilirubin, triglyceride, cholesterol, very low density lipoprotein, high density lipoprotein, low density lipoprotein, calcium, phosphorus, glucose
  - Urinary analysis: white blood cells per high power field (WBCs/HPF) and red blood cells per high power field (RBCs/HPF)
  - 24-hour UPE

- Pathological features: percentage of glomeruli with global glomerulosclerosis, percentage of glomeruli with segmental glomerulosclerosis, mesangial hypercellularity, endocapillary hypercellularity, tubular atrophy/interstitial fibrosis, percentage of glomeruli with crescents; MEST-C Oxford Score.

## **6.2. Distribution of the specified clinical variables at each visit**

To calculate and plot the group means and SDs of blood pressure (SBP, DBP, MAP), 24h urine protein excretion, and eGFR of the two treatment groups at each visit. LOCF will be used to fill the missing values.

## **6.3. Efficacy Analyses**

### **6.3.1. Main Analyses of the Primary Outcomes**

- The number of the composite outcome (primary outcome 1) and its components by each treatment group in ITT.
- The number of disease progression (primary outcome 2) by each treatment group in ITT.
- Kaplan-Meier curves of cumulative survival rates of the two primary outcomes by two treatment groups in ITT.
- To perform log-rank tests on the two primary outcomes between the two treatment groups in ITT. A p-value of 0.025 will be regarded as statistically significant.
- Estimate the hazard ratios (and 95% confidence intervals) of the treatment for the two primary outcomes, respectively, using the Cox proportional hazard models, with and without covariate adjustment. The adjusting covariates include age, sex, BMI, SBP, eGFR, logarithm of UPE rate and individual Oxford MEST-C scores at baseline.

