#### 7.4 Sample size

The sample size is estimated before the study with the use of nQuery Advisor software. Our preliminary study of IgA nephropathy showed that the three-year rate of the primary endpoint (doubling of serum creatinine, end-stage renal disease, and death) among patients with IgA nephropathy taking RAS inhibitors was 36%. It is estimated that MMF treatment will reduce this rate to 16%. Thus, the enrollment of 76 per group will provide the study with a statistical power of 80% at a two-sided significance level of 0.05. Considering 10% of participants lost to follow-up over 3 years, the final sample size was 84 per group.

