## 3.4. Primary Outcomes

There are two primary outcomes.

1. The time to the first event of the composite outcomes, including:
  - a doubling of serum creatinine, defined as serum creatinine doubled over the baseline and confirmed by another measurement at least four weeks apart; or
  - onset of end stage kidney disease, defined by the need for maintenance dialysis or renal transplantation or kidney failure (defined as  $\text{eGFR} < 15 \text{ ml/min/1.73m}^2$  and need for dialysis or renal transplant, but renal replacement therapy is not available or patients refuse to receive renal replacement therapy); or death due to kidney or cardiovascular cause.
2. The time to progression of CKD, defined by a sustained  $\geq 30\%$  decrease in eGFR and to a level of  $< 60 \text{ ml/min/1.73m}^2$  if the baseline eGFR was  $\geq 60 \text{ ml/min/1.73m}^2$ , or  $\geq 50\%$  decrease in eGFR if the baseline eGFR was  $< 60 \text{ ml/min/1.73m}^2$ . The CKD progression endpoints were also verified by another measurement at least four weeks apart.

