### **4.4. Multiplicity Adjustment**

For the primary analysis, a two-sided p value of <0.025 was regarded as statistically significant. For the secondary and safety analyses, no multi-test adjustment was employed, and a two-sided p value of <0.05 was regarded as statistically significant. The outcomes are clearly categorized by degree of importance (primary, secondary) and a limited number of subgroup analyses are pre-specified.

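### The two primary hazard ratios carry 95% intervals although each primary outcome is tested at two-sided 0.025, and the plan does not label those intervals as unadjusted for multiplicity

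*Combined protocol and SAP*

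**What the plan says.** SAP 3.4 states: "There are two primary outcomes". They are the kidney composite and progression of chronic kidney disease.

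SAP 4.4 sets the level: "For the primary analysis, a two-sided p value of <0.025 was regarded as statistically significant". It then treats the remaining analyses differently: "For the secondary and safety analyses, no multi-test adjustment was employed, and a two-sided p value of <0.05 was regarded as statistically significant".

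SAP 6.3.1 names the test, "To perform log-rank tests on the two primary outcomes between the two treatment groups in ITT", and repeats the threshold: "A p-value of 0.025 will be regarded as statistically significant". The next bullet of the same section asks the analyst to "Estimate the hazard ratios (and 95% confidence intervals) of the treatment for the two primary outcomes" from Cox models, with and without covariates.

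SAP 6.3.3.1 uses the same interval wording for a secondary outcome, the time to a 30% fall in eGFR, which is tested at 0.05. The interval level is therefore the same for an outcome tested at 0.05 and for two outcomes tested at 0.025. Neither document provides a 97.5% interval, describes the primary 95% intervals as descriptive or unadjusted, or says how to read an interval that disagrees with the log-rank result.

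**The concern.** A two-sided test at 0.025 corresponds to a 97.5% interval; a 95% interval corresponds to a test at 0.05. The sponsor has split 0.05 equally between two primary outcomes, but the interval that accompanies each effect estimate does not reflect the split.

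Many readers take the primary result from the hazard ratio and its interval. In a small trial with few expected events, a borderline result is realistic. The report could then state that an outcome missed its significance level beside an interval that excludes no effect, with no pre-specified sentence telling the reader which to rely on. What is at stake is the interpretation and presentation of the primary result, not the validity of the test.

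**Working it through.** **Inputs from the documents.** Two-sided level 0.025 per primary outcome (SAP 4.4, 6.3.1). Interval level 95% (SAP 6.3.1). Three-year rates of 36% (control) and 16% (MMF), 76 per group, 80% power at two-sided 0.05, and 84 per group after allowing for 10% loss (protocol 7.4). Allocation 1:1 (protocol 7.5).

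**1. The plan's own sample size.** With p1 = 0.36, p2 = 0.16 and mean 0.26, the pooled two-proportion formula gives

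n = [1.960 × √(2 × 0.26 × 0.74) + 0.842 × √(0.36 × 0.64 + 0.16 × 0.84)]² / 0.20² = 74.3, so 75 per group.

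The stated 76 is reproduced to within one patient; power at 76 is 80.9%. For loss to follow-up, 76 × 1.1 = 83.6, which rounds to the stated 84 (76 / 0.9 = 84.4 would round up to 85). The planning rates can therefore be used as stated.

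**2. Level of the tests.** 0.025 + 0.025 = 0.05, an equal Bonferroni split over two outcomes.

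**3. Critical values.** Two-sided 0.05: 1.960. Two-sided 0.025: 2.241. A result with |z| between them has p between 0.025 and 0.05: non-significant under the plan, with a 95% interval that excludes 1. The ratio 2.241 / 1.960 = 1.14 is the widening of a 97.5% interval on the log scale.

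**4. Events (assumption).** The documents give no event count. Applying the planning rates:
- 76 × (0.36 + 0.16) = 39.5, about 40
- 84 × (0.36 + 0.16) = 43.7, about 44

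**5. The zone as a hazard ratio.** With 1:1 allocation, SE(log HR) is about 2/√events. In favour of MMF, the limits are exp(−2.241 × SE) and exp(−1.960 × SE).

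| Events (assumed) | SE | HR at p = 0.025 | HR at p = 0.05 |
|---|---|---|---|
| 30 | 0.365 | 0.441 | 0.489 |
| 40 | 0.316 | 0.492 | 0.538 |
| 44 | 0.302 | 0.509 | 0.554 |
| 60 | 0.258 | 0.561 | 0.603 |

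**6. Probability of landing in the zone.** Under no effect: 0.05 − 0.025 = 2.5%, both tails together. For the design effect, exponential conversion gives HR = ln(0.84)/ln(0.64) = 0.391, so |log HR| = 0.940.
- 40 events: 0.940/0.316 = 2.972; Φ(2.972 − 1.960) − Φ(2.972 − 2.241) = 0.844 − 0.768 = 7.7%
- 44 events: 0.940/0.302 = 3.117; Φ(3.117 − 1.960) − Φ(3.117 − 2.241) = 0.876 − 0.809 = 6.7%

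**7. Example.** 44 events, |z| = 2.10, p = 0.036, HR 0.53. The 95% interval is 0.29 to 0.96; the 97.5% interval is 0.27 to 1.04.

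**8. Joint coverage.** Two 95% intervals: at least 1 − 2 × 0.05 = 90%. Two 97.5% intervals: at least 1 − 2 × 0.025 = 95%. The 90% is a lower bound. Independence gives 0.95² = 90.25%; for bivariate normal estimates with an assumed correlation of 0.8 or 0.9, coverage is about 92% or 93%.

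**The case against.** The strongest reply is that nothing in the SAP is violated. Significance rests on the log-rank p-value; the Cox bullet asks only for estimation, and a 95% interval is the conventional level for that. No text says that an interval excluding 1 means success, and none claims joint coverage. The threshold would also be reported beside the interval. All of this stands, and it limits the point to reporting.

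Three stronger readings are tempting but unsupported:
- **That the intervals overturn the decision rule or inflate the type I error.** They have no testing role in SAP 6.3.1, so the error rate of the two primary tests is what the 0.025 level gives.
- **That the conflict has about a 9% chance for each outcome.** That figure is the fall in power of a two-proportion test with 76 per group, from 80.9% at 0.05 to 72.1% at 0.025. The test here is log-rank and the interval comes from a Cox model, for which step 6 gives 6.7 to 7.7%. Moreover, protocol 7.4 gives 36% and 16% for the composite only.
- **That joint coverage is 90%.** This is the guaranteed floor. The two outcomes overlap, since both capture large losses of kidney function, so actual coverage should be higher.

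What the reply does not meet is the missing label. Unadjusted 95% intervals are acceptable when described as such, and here they are not.

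**Conclusion.** The point holds as a matter of reporting and interpretation. The test level reflects the split over two primary outcomes and the interval level does not, so the disagreement is systematic for every result with p between 0.025 and 0.05. For the composite, the chance of such a result is about 7 to 8% if the design effect is true.

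The size rests on assumed counts of 40 to 44 events, the approximation SE = 2/√events, and exponential conversion of the three-year rates. With 30 or 60 events the zone moves as tabulated. For progression of chronic kidney disease the mismatch is the same in kind, but without a stated rate or effect it cannot be sized.

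The correction is worth making because it is cheap and must be settled before results are known.

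**What to change.** In SAP 6.3.1, specify 97.5% confidence intervals for the hazard ratios of the two primary outcomes, as the intervals matched to the 0.025 level. If 95% intervals are also wanted, label them as unadjusted for multiplicity and not used to judge significance. At the least, add that label to the existing 95% intervals; this removes the ambiguity but leaves the interval and the test at different levels.

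The cost is one line of text and intervals about 14% wider on the log scale. Data, sample size and conduct do not change. Small disagreements can remain, because the log-rank test and a Cox interval, above all a covariate-adjusted one, need not agree exactly at the same level. The SAP could add that the log-rank result decides in such a case.
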